**Figure 1 fig1:**
[figure not shown]
ASCEND-VT trial flowchart. AE = adverse event; PFA = pulsed field ablation; RFA = radiofrequency ablation.

### Baseline data collection

During the baseline office visit (or inpatient interview), data will be collected including patient medical history, demographics, and medication regimen. In particular, this will include physical and cardiac assessment, cardiovascular disease history, cerebrovascular disease history, cardiac procedure history, atrial and ventricular arrhythmia history, subject comorbidities, pandemic history, and information on antiarrhythmic (class I and III) and anticoagulation medications.

Further testing such as electrocardiogram and echocardiogram will be performed. The 36-item short form health survey will be administered.

Device interrogation will be performed, and information including the description of the last 10 VT episodes and resulting treatment (rate, duration, antitachycardia pacing/shock before enrollment, programming of therapy zones, etc) will be collected.

### Ablation procedure: General considerations

In both study arms, the ablation procedure will be done under general anesthesia or conscious sedation (with local anesthesia administered to the vascular access sites), per individual operator’s preference. Antithrombotic agents will be continued or held before the procedure at the primary operator’s discretion. Femoral intravascular access will be obtained under ultrasound guidance. Intracardiac echocardiography and a quadripolar right ventricular pacing catheter will be used in all cases. A multipolar mapping catheter and an ablation catheter (see below) will be advanced into the LV via transseptal or retroaortic approach, as deemed appropriate by the operator.

### Ablation procedure: Baseline inducibility

Baseline programmed ventricular stimulation (PVS) will be performed at the start of the procedure. This will entail using up to 3 extrastimuli down to the ventricular effective refractory period or coupling intervals of 200 ms (whichever occurs sooner) or until VT or ventricular fibrillation is induced. The use of multiple drive train cycle lengths (eg, 600 and 400 ms) and at least 2 pacing sites (eg, right ventricle and LV) is encouraged.

Any induced sustained monomorphic VT will be recorded; activation mapping of hemodynamically stable VT is permissible at this point, but ablation should not be performed. Sustained VT should be terminated using overdrive pacing or external cardioversion.

### Ablation procedure: Substrate mapping

In the control arm, the choice of mapping system and mapping catheters will depend on the operator’s discretion using a commercially available electroanatomic mapping system and mapping catheter. In the intervention arm, mapping will be done using the OPAL HDx mapping system (Boston Scientific, Marlborough, MA) along with the ORION multipolar basket catheter (Boston Scientific). Ablation catheters (outlined below) may also be used for mapping in all patients.

In both study arms, substrate mapping will be done during sinus rhythm and/or paced rhythm.

### Ablation procedure: Definition of substrate target

The main substrate ablation target will be LAVA electrograms within the abnormal substrate. These are defined as sharp high-frequency ventricular potentials, possibly of low amplitude, distinct from the far-field ventricular electrogram occurring any time during or after the far-field ventricular electrogram in sinus/paced rhythm that sometimes display fractionation or double or multiple components separated by very-low-amplitude signals or an isoelectric interval and are poorly coupled to the rest of the myocardium.^15^ During substrate mapping, all sites with LAVAs will be marked using the mapping system. In addition, in patients with stable VTs, activation and entrainment mapping will be permitted to prioritize LAVA areas to target, whereas, in patients with unstable VTs, pace mapping from substrate areas with LAVAs will also be permitted.

### Ablation procedure: Substrate ablation

All LAVA areas will be targeted for ablation unless concern for collateral damage is thought to outweigh the benefits by the operator (eg, vicinity of conduction system). Ablation should not be performed in the proximity of metallic devices (such as intracardiac lead electrodes) to avoid arcing, cardiac trauma, and/or damage to the devices.

In the control arm, ablation will be done using commercially available contemporary RFA contact force–sensing slow-flow irrigated RFA catheters using standard irrigation settings and 30–50 W output for at least 30 seconds. The goal of each lesion will be the complete elimination of LAVA and/or local myocardial noncapture during high-output pacing (10 mA/2 ms to 20 mA/2 ms).

In the intervention arm, PFA will be done via the FARAPOINT focal catheter (Boston Scientific) using 5 bipolar/biphasic trains of 2.0 kV applications delivered over 2.5 seconds; the number of applications will be repeated based on lesion depth needs. There will be no limit on the number of RFA or PFA lesions.

In both study arms, the ablated areas will be remapped using the same catheter used for baseline substrate mapping and elimination of LAVAs will be confirmed by the primary operator (post hoc data review by the principal investigators [[name] and [name]] to confirm LAVA elimination will also be performed, and any discrepancies will be documented). In addition, high-output pacing (10 mA/2 ms to 20 mA/2 ms) will be delivered to the ablated sites to confirm noncapture at high or very high output. If persistent LAVAs and/or locations with persistent myocardial capture are identified, additional ablation is encouraged in both study arms.

Patients with an anticipated need for epicardial access will be excluded from the study. However, in cases where ad hoc epicardial access becomes necessary in an enrolled study subject (eg, unexpected identification of an epicardial VT focus during the procedure), epicardial mapping/ablation can be performed as clinically necessary; however, only RFA ablation is permitted in the pericardial space (or inside the coronary sinus system).

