**Conclusion:**

This is the first pilot randomized controlled trial comparing the safety and efficacy of focal PFA vs RFA VT ablation in ICM. Its results will inform the design of future larger studies that will further establish the clinical utility of PFA in the context of scar-related VT ablation.

Key Findings
▪ASCEND-VT is a pilot trial that randomizes patients with ischemic cardiomyopathy and ventricular tachycardia to endocardial ablation using standard radiofrequency vs novel pulsed field ablation catheter.▪The intervention arm will use the new FARAPOINT focal pulsed field ablation catheter (under the US Food and Drug Administration’s investigational device exemption).▪The immediate procedural endpoint in all patients will be total elimination of abnormal electrograms, specifically late abnormal ventricular activity (LAVA).▪The trial’s primary efficacy metric is the time needed to eliminate LAVAs in the 2 study arms. This will be tested for noninferiority.▪Additional efficacy and safety metrics will be assessed after the ablation and over the course of a 6-month follow-up period.

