### Endpoints

The efficacy and safety endpoints are presented in Table 3. In brief, the primary efficacy endpoint is the total time needed to ablate and eliminate all targeted LAVAs. The secondary efficacy endpoints include other procedural metrics (including postprocedural inducibility, total procedural duration, and fluid balance) and time-dependent outcome metrics such as total mortality, hospital admissions for cardiovascular indication, and recurrences of VT/ventricular fibrillation. Safety endpoints include a range of possible periprocedural complications, with particular attention paid to issues that may be more relevant to PFA; this includes any coronary events (including coronary vasospasm), acute kidney injury, and changes in LVEF and/or evidence of new wall motion abnormalities.

**Table 3 tbl3:** Efficacy and safety endpoints

Primary efficacy endpoint	Objective/rationale
Time needed to eliminate LAVAs	This is the primary procedural efficacy metric highlighting a key potential advantage of PFA over RFA technology.
Acute secondary efficacy endpoints	Objective/rationale
Total procedural duration	These are additional procedural efficacy metrics expected to mirror the primary efficacy endpoint.
Total fluid administered by the ablation catheter	
Total fluid administered during the procedure	
Fluid balance at the end of the procedure	
Ongoing presence of LAVAs at the end of the procedure	A different efficacy metric. LAVA elimination may not always be possible with RFA and is likely always feasible with PFA, although the durability of this elimination remains to be determined.
VT noninducibility at the end of the procedure	A standard acute endpoint metric, although its utility has lately been challenged^45^
Time-dependent secondary efficacy endpoints (assessed 6 mo postoperatively)	Objective/rationale
Recurrences of sustained VT leading to appropriate ICD interventions (ATP or shock) or any symptomatic sustained VT	Standard clinical follow-up endpoints. The ASCEND-VT trial is not powered to show significant differences in these outcomes. However, if major differences are ultimately observed in these metrics, future studies will have to elucidate whether the procedural workflow of PFA needs to be adjusted.
Any documented sustained VT below the detection rate of the ICD	
All-cause mortality	
VT burden (number of appropriate ICD therapies in the 6 mo before ablation vs 6 mo after the ablation)	
Hospital admissions for cardiovascular causes	

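### The primary time ends on the judgement of an operator who knows the arm, and the only stated consequence of the planned second review is that disagreements are recorded

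*Protocol article*

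**What the plan says.** The Endpoints section states that "the primary efficacy endpoint is the total time needed to ablate and eliminate all targeted LAVAs", and the Key Findings box likewise says that the "primary efficacy metric is the time needed to eliminate LAVAs in the 2 study arms".

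The section on substrate ablation sets out how elimination is established in both arms:

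- The ablated areas are remapped with the catheter used for the baseline map, and "elimination of LAVAs will be confirmed by the primary operator".
- High-output pacing "will be delivered to the ablated sites to confirm noncapture at high or very high output".
- If LAVA or capture persists, "additional ablation is encouraged in both study arms". It is not required.
- The operator also has a say in what counts as targeted: "All LAVA areas will be targeted for ablation unless concern for collateral damage is thought to outweigh the benefits by the operator".
- A post hoc data review by the principal investigators "to confirm LAVA elimination will also be performed", and "any discrepancies will be documented".

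Table 3 lists LAVAs still present when the procedure ends as an acute secondary endpoint and names no assessor. The statistical section plans a two-sample t test on the time to complete elimination.

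**The concern.** A time-to-success endpoint depends on who decides that success has occurred. Here it is the person using the device. That person knows the arm and works in a trial whose Introduction states the expectation that PFA will be faster. Deciding that a low-amplitude or fractionated potential has gone takes judgement.

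The plan already includes a second look, which is the natural safeguard. The article, however, connects that look to no endpoint and no analysis. If the review finds that LAVA was still present, the recorded time is a time to an event that did not happen, yet nothing stated stops it from being analysed as a completed elimination. If such cases were unevenly spread between the arms, the comparison of times would partly reflect when operators chose to stop and not only how fast the technology works.

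**Working it through.** **Step 1. What ends the clock.** The Endpoints section describes time to ablate and eliminate; the statistical section speaks of total ablation time. On either reading, the last contribution to the time is made when the operator judges that no targeted LAVA remains.

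**Step 2. Whether the operator knows the arm.** The article does not use the word unblinded, but it follows from the equipment. The PFA arm uses one named focal catheter and one named mapping system. The control arm uses commercial irrigated RFA catheters and a mapping system of the operator's choice.

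**Step 3. What limits the judgement.** There are three checks: an electrogram definition of LAVA with all sites marked at baseline, remapping with the same catheter, and pacing at 10 to 20 mA/2 ms to show noncapture. They leave recorded data. The article names no other reader during the case, does not oblige further ablation when they are positive, and does not make noncapture part of the primary endpoint.

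**Step 4. What the review leads to.** The statements on the review, the endpoint and the t test give one consequence for a disagreement: documentation. No rule reclassifies the patient, alters the time or calls for a sensitivity analysis. The normalization to baseline LAVA area in the Discussion deals with differences between mapping systems, not with when the operator stops.

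**Step 5. Scale.** No figure in the article depends on this point, so there is none to correct. The plan's own sample size serves only to calibrate an illustration.

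- Withdrawal allowance: 36 / (1 − 0.10) = 40, as stated.
- The 18 per arm cannot be reproduced directly, because no SD is given. At 80% power and two-sided 0.05, a t test with 18 per arm detects a standardized difference of 0.961. A 50% difference then implies a common SD of 0.5 / 0.961 = 0.52 of the control mean. (One-sided: 0.5 / 0.846 = 0.59.)
- Assume SD 0.52 of the control mean, no true difference, 18 per arm and two-sided 0.05. If the operator's call shortened mean PFA time by a fraction b, the standardized shift would be b / 0.52:

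| b (assumed) | b / 0.52 | Chance of a significant result |
|---|---|---|
| 5% | 0.10 | about 6% |
| 10% | 0.19 | about 9% |
| 20% | 0.38 | about 20% |
| 30% | 0.58 | about 39% |

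- If PFA truly halves the time, a 10% shortening would show as 1 − 0.5 × 0.9 = 55% instead of 50%.
- Residual-LAVA endpoint: one patient of 20 is 1/20 = 5 percentage points.

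The values of b are assumptions; the article supports none of them. The table shows only that a small distortion matters little and a moderate one does not.

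**The case against.** Several counter-arguments carry weight.

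- **The article is condensed.** A reader might infer that the review has no effect at all. The article does not say so. It says what happens to a disagreement and is silent on the rest; a full protocol or SAP, not shown here, may link the review to the analysis. What stands is narrower: the one consequence the article fixes is documentation.
- **The endpoint is not purely subjective.** Baseline marking, same-catheter remapping and pacing constrain the operator. This stands and lowers the concern, but the same operator interprets them.
- **Direction of bias.** A reader might infer that the comparison is tilted towards PFA. The documents do not support that. An expectation of speed could lead to earlier stopping with PFA, but caution with an investigational catheter could lead to extra applications.
- **Residual-LAVA endpoint.** A reader might infer that it carries the same error. Table 3 names no assessor, so the review may already be its intended source.
- **The reviewers are not independent.** They are the principal investigators and can tell the arm from the mapping system. Making their reading decisive for the primary endpoint would replace one unmasked judge with another and would still supply no time for a patient judged not eliminated. This stands, and it is why the reviewed status belongs in a sensitivity analysis.
- **It is a pilot, and operators cannot be masked.** Both are true. But the primary comparison is a formal test at 0.05 with 80% power, and the remedy does not ask for masked operators.

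**Conclusion.** The point holds in a limited form. An operator who knows the arm ends the primary time. The review that could show whether elimination was achieved has, as stated, no analytic consequence, so a patient with residual LAVA on review would still contribute a completed elimination time.

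Neither the size nor the direction of any bias can be derived from the article. The illustrative rates rest on an assumed SD of 0.52 of the control mean, no true difference and assumed shortening of 5% to 30%. They are not a prediction. If the true difference is near the 50% the plan expects, modest early stopping would be unlikely to change the conclusion that PFA is faster; it would matter more if the true difference were small.

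This is an inexpensive improvement to the use of data already being collected, not a flaw that invalidates the primary comparison. If an unseen SAP already contains such a rule, confirming it settles the point.

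**What to change.** 1. State that LAVA status on the planned review defines the residual-LAVA secondary endpoint.
2. Keep the operator-based time as the primary analysis. Prespecify a sensitivity analysis in which patients with residual LAVA at targeted sites on review count as not eliminated. They could be censored at the operator's stop time in a time-to-event comparison, or given the worst rank in a rank-based test. Choose one in advance. The worst-rank version avoids assuming that censoring is unrelated to how hard the substrate was to ablate.
3. Have the reviewers read the final maps and electrograms without the recorded time and, as far as the two existing reviewers allow, not review their own cases.
4. Report operator–reviewer agreement by arm.

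**Cost.** Wording in the SAP and review instructions, plus a little more analysis. No new reader is needed, and the sample size does not change. Because the mapping systems differ between the arms, the reviewers cannot be fully masked, so the change reduces the risk of bias but does not remove it.

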### Ablation procedure: Subsequent inducibility

PVS will be repeated in hemodynamically stable patients using the same protocol as before (when testing for baseline inducibility). Mapping and ablation of any sustained VT (thought to be clinically relevant and/or exhibiting tachycardia cycle length of ≥240 ms) will be encouraged using any strategy deemed suitable by the operator. If clinically appropriate, PVS will then be repeated until no further sustained VT (meeting the criteria mentioned earlier) is inducible. Cross-over to the other study arm at this point will be considered a protocol deviation.

### Postprocedural care

All study subjects will receive standard postprocedural care that will include observation for at least 1 night. Most medical management decisions, including the use of antithrombotic agents, will be left up to the discretion of the primary operator. At most 1 antiarrhythmic drug can be used for up to 1 month after ablation when it will be discontinued. ICD programming in the individual patient should be evaluated and verified after the procedure to allow for similar detection and treatment of VT as before the procedure. ICD interrogation will also include a review of lead parameters, and any deviation from preablation values will be recorded.

### Follow-up

The outline of the follow-up data collection strategy is presented in Table 2. Primary and procedural efficacy along with adverse event review will be performed immediately after the procedure and at the time of hospital discharge. Study visits 1 (7-40 days after the procedure) and 2 (90 ± 30 days after the procedure) will include functional assessment, ICD interrogation, and adverse event review. The final study visit (day 180 ± 30 after the procedure) will be a comprehensive assessment that will include transthoracic echocardiography and the 36-item short form health survey.

**Table 2 tbl2:** Schedule of activities

Procedures	Screening and enrollment/baseline, day −90 to −1	Ablation procedure	Discharge	Study visit 1, day 7–40∗	Study visit 2, day 90 ± 30∗	Final study visit, day 180 ± 30
Informed consent	X					
Demographics	X					
Medical history	X					
Physical examination	X		X			X
NYHA assessment	X			X	X	X
Vital signs	X		X			X
TTE†	X					X
ECG	X					X
ICD interrogation‡	X	X		X	X	X
SF-36	X					X
Adverse event review and evaluation		X	X	X	X	X
Complete case report forms	X	X	X	X	X	X

ECG = electrocardiogram; ICD = implantable cardioverter-defibrillator; NYHA = New York Heart Association; SF-36 = 36-item short form health survey; TTE = transthoracic echocardiogram.

∗ In-office visit or telephone/virtual visit. ICD interrogation can be monitored remotely.

† TTE at baseline to be performed within 6 months of enrollment.

‡ ICD interrogation can be performed via remote monitoring.

### Endpoints

The efficacy and safety endpoints are presented in Table 3. In brief, the primary efficacy endpoint is the total time needed to ablate and eliminate all targeted LAVAs. The secondary efficacy endpoints include other procedural metrics (including postprocedural inducibility, total procedural duration, and fluid balance) and time-dependent outcome metrics such as total mortality, hospital admissions for cardiovascular indication, and recurrences of VT/ventricular fibrillation. Safety endpoints include a range of possible periprocedural complications, with particular attention paid to issues that may be more relevant to PFA; this includes any coronary events (including coronary vasospasm), acute kidney injury, and changes in LVEF and/or evidence of new wall motion abnormalities.

**Table 3 tbl3:** Efficacy and safety endpoints

Primary efficacy endpoint	Objective/rationale
Time needed to eliminate LAVAs	This is the primary procedural efficacy metric highlighting a key potential advantage of PFA over RFA technology.
Acute secondary efficacy endpoints	Objective/rationale
Total procedural duration	These are additional procedural efficacy metrics expected to mirror the primary efficacy endpoint.
Total fluid administered by the ablation catheter	
Total fluid administered during the procedure	
Fluid balance at the end of the procedure	
Ongoing presence of LAVAs at the end of the procedure	A different efficacy metric. LAVA elimination may not always be possible with RFA and is likely always feasible with PFA, although the durability of this elimination remains to be determined.
VT noninducibility at the end of the procedure	A standard acute endpoint metric, although its utility has lately been challenged^45^
Time-dependent secondary efficacy endpoints (assessed 6 mo postoperatively)	Objective/rationale
Recurrences of sustained VT leading to appropriate ICD interventions (ATP or shock) or any symptomatic sustained VT	Standard clinical follow-up endpoints. The ASCEND-VT trial is not powered to show significant differences in these outcomes. However, if major differences are ultimately observed in these metrics, future studies will have to elucidate whether the procedural workflow of PFA needs to be adjusted.
Any documented sustained VT below the detection rate of the ICD	
All-cause mortality	
VT burden (number of appropriate ICD therapies in the 6 mo before ablation vs 6 mo after the ablation)	
Hospital admissions for cardiovascular causes	
Primary safety endpoints (assessed ≤7 d postoperatively)	Objective/rationale
Cardiac perforation	Benchmark safety data from the ThermoCool VT trial^10^ were based on similar endpoints.
Pericardial effusion with hemodynamic compromise or needing intervention	
New complete heart block	
Coronary spasm	
Acute MI	
New acute severe mitral regurgitation or aortic regurgitation	
Deep venous thrombosis	
Vascular injury requiring surgical or percutaneous intervention	
Pulmonary embolism	
Stroke	
Acute kidney injury (>0.5 mg/dL increase in creatinine from baseline within 24 h after the procedure)	
Death	
Secondary safety endpoints (assessed during follow-up)	Objective/rationale
Device- or procedure-related SAEs (the proportion of subjects in each treatment arm with at least 1 device- or procedure-related SAE)	Summary metric of SAE frequency
Acute kidney injury	Metrics of particular relevance to the PFA technology
Coronary vasospasm at any point during follow-up	
Changes in LVEF and/or new wall motion abnormalities at follow-up TTE (180 d)	

ATP = antitachycardia pacing; ICD = implantable cardioverter-defibrillator; MI = myocardial infarction; LAVA = late abnormal ventricular activity; LVEF = left ventricular ejection fraction; PFA = pulsed field ablation; RFA = radiofrequency ablation; SAE = serious adverse event; TTE = transthoracic echocardiogram; VT = ventricular tachycardia.

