Pulsed field ablation (PFA) is primarily a nonthermal ablation technique that causes cell death by creating pores in myocyte membranes.^21^^,^^22^ Although the nominal dimensions of the myocardial PFA lesions may be comparable with RFA, the former may be more efficient and consistent in creating lesions in scarred substrate.^23^, ^24^, ^25^ Just as importantly, in contrast to RFA, PFA lesions can be created much more rapidly (typically <10 seconds per site) and with the use of minimal or no irrigation. In contrast, the use of PFA may be associated with an increased risk of certain adverse events that are relatively specific to this technology; as shown in ablation studies targeting atrial arrhythmias, this includes the risk of coronary vasospasm and hemolysis-related acute kidney injury.^26^^,^^27^ Even so, the recently published aggregate ADVANTAGE AF data suggest that the overall safety profile for atrial PFA ablations is very favorable (primary safety endpoint rate 2.0%; myocardial infarction rate 0.2%; and clinically relevant hemolysis rate 0.6%, although no events required hemodialysis).^28^

Several small studies and case reports have examined the safety and efficacy of PFA in the context of VT ablation.^29^, ^30^, ^31^, ^32^, ^33^, ^34^ Larger cohort data on PFA ablation of VT and premature ventricular contractions have only been published recently. This includes our own experience with a large-footprint pentaspline PFA catheter (n = 11)^35^ and a larger series by Ruwald et al^36^ (n = 35) that relied on a focal ablation catheter and PFA generator. The outcomes in VT ablation were similar to what was previously reported with focal RFA catheters. In particular, Ruwald et al^36^ saw a 55% 1-year recurrence rate in VT ablation patients. However, it is important to state that the studied population was enriched for high-complexity cases with intricate, nonischemic substrate. Although the complication rates in these (and other) studies are reassuring,^35^, ^36^, ^37^ the safety of PFA is yet to be confirmed in a more uniform population.

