### Statistical analysis and power calculations

The primary null hypothesis is that the total ablation time needed for complete LAVA elimination (ie, primary efficacy metric) will not be different between the 2 study arms. This hypothesis will be tested using a 2-sample *t* test.

PFA lesion delivery time will be, by design, shorter (3 2.5-second pulse trains = 7.5 seconds per ablation site) than RFA (at least 30 seconds per lesion). Furthermore, effective RFA lesion dimensions may vary widely depending on the distribution of myocardial scar, whereas PFA lesions are expected to be more consistent.^25^^,^^38^ Therefore, we envisage the time needed to eliminate targeted LAVAs to differ by at least 50% between the 2 study arms. With a desired power of 80% and a significance level of 0.05, the predicted minimum enrollment is 36 patients (18 in each study arm). This will be increased to 40 patients to allow for a 10% withdrawal rate. 10 additional patients will be screened to allow for possible screen failures.

The secondary efficacy and both primary and secondary safety endpoints will be analyzed using *t* test, rank sum test, or Fisher’s exact test, as appropriate. Time-dependent outcomes will be analyzed as landmark events. However, if the event rates and/or dropout rates are high in either group (≥20%), time-to-event methodology will be adopted (Cox regression and Fine-Gray competing risk models, as appropriate). Univariate and multivariable models will be used.

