The ASCEND-VT study will also look at hard clinical outcomes such as VT recurrences and all-cause mortality, although the power to detect any signal in this realm may be limited. Indeed, establishing overall clinical noninferiority of 1 ablation technology over another, for example, proving that the use of PFA results in lower VT recurrence or lower mortality than RFA, will necessitate a large-scale multicenter trial with an extended follow-up time. However, ASCEND-VT will provide important early information to design a large head-to-head comparative trial.

The ASCEND-VT study is also intended to systemically assess the safety of PFA in ICM VT ablations. Although the rate of vascular or major mechanical cardiac adverse events (eg, pericardial effusion and tamponade) is expected to be comparable between the 2 study arms, certain potential complications are relatively specific to PFA and will need to be separately assessed. First, early PFA literature (particularly in the context of atrial ablation) has shown that transient hemolysis is a relatively frequent consequence of PFA ablation, although the incidence of resulting end-organ damage is very low.^28^^,^^41^^,^^42^ For this reason, the ASCEND-VT trial will specifically track the rate of acute kidney injury after the procedure. Second, PFA in the atrium may result in vasospasm when applied in the vicinity of coronary arteries^26^^,^^43^; although patients in ASCEND-VT will only be subjected to ventricular endocardial PFA applications (ie, not near the epicardial coronary vessels), the possibility of vasospasm with or without substantial myocardial injury will be closely tracked. However, the potential for vasospasm is not unique to PFA alone, having previously been demonstrated with RFA, and will be evaluated in both arms. Third, even in the absence of new coronary injury, there is a theoretical concern that the uniform and large PFA lesions may have an effect on myocardial contractility, especially if applied outside of noncontractile scar^44^; therefore, the ASCEND-VT trial will pay particular attention to any perturbations in LVEF and/or evidence of new wall motion abnormalities after ablation.

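### Renal safety is compared only through a yes/no AKI event, which with 20 patients per arm is close to uninformative; the creatinine change that the definition already requires should be compared as well

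*Protocol article*

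**What the plan says.** Table 3 of the protocol article (Endpoints) lists among the primary safety endpoints, assessed up to 7 days after the procedure: "Acute kidney injury (>0.5 mg/dL increase in creatinine from baseline within 24 h after the procedure". The rationale given for that list is comparability with an earlier RFA trial in VT.

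Acute kidney injury appears again among the secondary safety endpoints, assessed during follow-up, under the rationale "Metrics of particular relevance to the PFA technology". No threshold, time or scale is given there.

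On tests, Statistical analysis and power calculations says: "The secondary efficacy and both primary and secondary safety endpoints will be analyzed using" a t test, a rank-sum test or Fisher's exact test, whichever is appropriate.

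The Discussion gives the reason for the renal endpoint. It says that "transient hemolysis is a relatively frequent consequence of PFA ablation, although the incidence of resulting end-organ damage is very low", and continues: "For this reason, the ASCEND-VT trial will specifically track the rate of acute kidney injury after the procedure". The Introduction reports, for atrial PFA, a "clinically relevant hemolysis rate 0.6" per cent.

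The article names no analysis of creatinine on its own scale and no laboratory marker of haemolysis.

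**The concern.** Renal injury from haemolysis is one of the few PFA-specific risks that the article says must be assessed separately, and the trial is meant to inform the design of a larger one. The endpoint is a cut of a continuous measurement, and a high cut: by the article's own account overt organ damage is very uncommon. A rate is a proportion, so of the three tests offered the appropriate one is Fisher's exact test.

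With 20 patients per arm and rare events, that comparison can say very little. Zero or one event in each arm is the likely result whether or not PFA raises creatinine moderately, and it could be carried into the next trial as reassurance. The baseline and within-24 h creatinine values needed for a more informative comparison must be obtained anyway to apply the definition.

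**Working it through.** **Inputs from the article.** 40 patients randomized 1:1, so 20 per arm (Trial design). AKI is a creatinine rise above 0.5 mg/dL within 24 h (Table 3). The only related rate is 0.6% for clinically relevant haemolysis in atrial PFA (Introduction). The article gives no AKI rate, creatinine SD or power for AKI, so there is no stated figure to reproduce; the 36 patients in the power paragraph concern ablation time.

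**Assumptions.** Two-sided 5% level. AKI rates over a range. For the continuous scale, a normal creatinine change with the same SD in both arms, shifted upward in every PFA patient.

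**1. What Fisher's test can detect at 20 per arm.**
- 4 vs 0: p = 0.106.
- 5 vs 0: p = 0.047.
- With one RFA event, 7 PFA events are needed (p = 0.044); with two, 9 (p = 0.031).
- With an RFA rate of 0.6%, the PFA rate would have to be about 33% for 80% power.

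**2. What a count of zero would mean.** The chance of no event among 20 PFA patients is (1 − p)^20: 0.89 at p = 0.6% and 0.67 at p = 2%. After 0 of 20, the two-sided 95% upper limit is 1 − 0.025^(1/20) = 16.8%.

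**3. Information kept by the cut.** For an exceedance rate p, with c = z(1 − p), the efficiency relative to the uncut measurement under a normal shift is φ(c)² / [p(1 − p)].

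| Rate p | c | φ(c) | Kept | Lost |
|---|---|---|---|---|
| 0.6% | 2.512 | 0.0170 | 4.8% | 95% |
| 2% | 2.054 | 0.0484 | 12.0% | 88% |
| 5% | 1.645 | 0.1031 | 22.4% | 78% |
| 10% | 1.282 | 0.1755 | 34.2% | 66% |

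For example, at 2%: 0.0484² / (0.02 × 0.98) = 0.120.

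**4. Power, 20 per arm.** The shift in SD units is d = z(p_PFA) − z(p_RFA), with z the normal quantile. Fisher's power is by full enumeration. Rank-sum power uses the noncentral t distribution with efficiency 0.955.

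| AKI, RFA vs PFA | d | Fisher on the cut | Rank-sum on the change |
|---|---|---|---|
| 1% vs 5% | 0.68 | 0.2% | 54% |
| 2% vs 10% | 0.77 | 3% | 64% |
| 5% vs 20% | 0.80 | 17% | 68% |

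Simulation with 20,000 replicates for 2% vs 10% agrees: about 3% and 63 to 64%.

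**5. Size of these shifts.** If the mean RFA change is zero and 2% exceed 0.5 mg/dL, the SD is 0.5 / 2.054 = 0.24 mg/dL, so 0.77 SD is about 0.19 mg/dL. That is a moderate shift. For a shift of only 0.3 SD, simulated power is below 1% for Fisher and about 14% for the rank-sum test.

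**6. A different pattern of harm.** Suppose most PFA patients are unaffected and a few have a large rise (+4 SD), with RFA at 2%. With 8% affected, simulated power is about 3% for Fisher and 7% for the rank-sum test. With 13% affected, it is about 11% and 10%. The gain largely vanishes, but there is no material loss.

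**The case against.** **The event is legitimate.** AKI is a clinically meaningful safety event, the primary item has a stated benchmark, and no power is claimed for it. The article also concedes that uncommon complications may not be estimable. All of this stands. A reader might infer that the 0.5 mg/dL definition is wrong or should be dropped; nothing in the article supports that.

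**The shift pattern is an assumption.** A reader might infer from frequent haemolysis and rare organ damage that PFA causes a small creatinine rise in many patients. The article does not say so. Its words fit equally well with no renal effect in most patients and a large rise in a few, where the continuous scale gains little. Nor would the continuous comparison reliably find a small shift. It helps with moderate ones.

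**The secondary item is undefined.** A reader might infer that it too is cut at 0.5 mg/dL and explicitly assigned to Fisher's test. The cut is attached to the primary item only, and the three tests are listed for the safety endpoints together. The event reading of the follow-up item rests on its name and on the Discussion's reference to a rate. Table 2 lists no creatinine measurement at follow-up visits, so replacing this item by a creatinine change is not a free rewording.

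**Fluid differs between the arms.** The Introduction describes substantial irrigation volumes with RFA and minimal or none with PFA. Dilution could lower early creatinine in the RFA arm and make PFA look worse. This stands as a limit on interpretation. It affects the AKI cut too.

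**The article is condensed.** The full protocol may contain more. The scale of the renal comparison is nevertheless stated here, as an event and a rate, and is not merely left open.

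**Conclusion.** The concern holds in a limited form. As written, the renal comparison rests on an event count that needs about 5 vs 0 to reach significance, and across the assumed rates in step 4 it has 0.2 to 17% power where a rank-sum test on the change would have 54 to 68%. The loss of information is 88 to 95% at AKI rates of 0.6 to 2% and 66 to 78% at 5 to 10%, so describing it as almost all of the information is fair only at the low end.

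These figures rest on assumed AKI rates and on a uniform normal shift. If harm is a rare large rise, there is little to gain and nothing material to lose. The point is a cheap gain in precision on a safety question that the article itself singles out. It is not an error in the AKI definition.

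**What to change.** Keep both AKI items and their counts as they are. Add one supportive safety analysis: the between-arm comparison of creatinine change from baseline to the value within 24 h that the AKI definition already requires. Use the rank-sum test with the Hodges-Lehmann shift and its 95% confidence interval, or a baseline-adjusted comparison; fix one of the two in advance. Do not substitute it for the follow-up AKI item.

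State with it that a shift in creatinine is not clinical kidney injury, and that it is to be read beside catheter fluid, total fluid and fluid balance, which Table 3 already records, because of possible dilution in the RFA arm.

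The cost is a sentence or two of analysis text and one more safety estimate to report and interpret. No additional blood test is needed beyond those that the AKI definition implies.
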